#### Blinding

Due to the nature of the treatment conditions, it is impossible to blind the staff and participants throughout the study. However, the baseline assessment will be conducted while participants as well as staff are blinded.

### Intervention and control

#### Intervention

The intervention will consist of the smoking cessation program designed and adapted for food pantry users in the pre study as well as optional nicotine replacement therapy and the implementation of environmental smoking reduction measures in the food pantries.

The intervention will be provided by trained and certified smoking cessation trainers.

During the group sessions, potential environmental measures to make the food pantry less smoker friendly (e.g. defined smoking areas) will be identified and potentially implemented.

In addition to the group counselling, participants will be provided nicotine replacement therapy free of charge if requested. The dosage of the nicotine replacement will be individually tailored according to the Fagerström Test for Nicotine Dependence [39, 40].

#### Control

The control group consists of a waiting group and will be provided with the usual food pantry supplies and will receive the intervention when the last data collection period is finished (after t2).

### Outcome measures and evaluation

#### Measures

At t0, participants will be asked to complete a survey containing questions on demographics, developed by a previous study among food pantry users in Germany [41]; the Short Form 12 (SF-12) to measure the quality of life [42]; the quantity-frequency index [37]; the Fagerström Test for Nicotine Dependence (FTND) [39, 40]; the Food Insecurity Experience Scale (FIES) [43]; and the future, present-hedonistic and present-fatalistic subscales of the Zimbardo Time Perspective Inventory [44, 45]. At t1 and t2 continuous abstinence will be measured according to the “Russell standard” (“Have you smoked at all since [start date of last attempt to quit]?” “No, not a puff”; “1–5 cigarettes”; “More than 5 cigarettes?”) [46].

In addition, exhaled carbon monoxide will be measured at baseline as well as at t1 and t2. The time points for the measurements are shown in Table 1.

**Table 1 Tab1:**
[figure not shown]
Time schedule of the cluster randomized trial

#### Outcomes

Primary outcomes are continuous smoking abstinence (yes or no; the percentage of participants with continuous smoking abstinence) and increased food security level (the percentage of participants with an improved food security level) 6 months after the treatment has finished. Smoking abstinence is defined as the self-reported continuous smoking cessation (≤ 5 cigarettes since the start date of their last attempt to quit) validated by the exhaled carbon monoxide test (< 10 ppm of carbon monoxide) [46]. Food insecurity is categorised into four groups: food security; mild food insecurity; moderate food insecurity; and severe food insecurity according to the Food and Agriculture Organization of the United Nations [21].

Secondary outcomes at one and 6 months post-intervention include the point prevalence of smoking abstinence, the mean number of cigarettes smoked per day, the mean number of affirmative responses on the FIES, and the health-related quality of life scores.

Time perspective will be investigated as moderator.

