## Background

Smoking is one of the major risk factors of mortality and morbidity in Germany [1] and accounts for around 125,000 premature deaths per year [2]. In addition to individual burden, smoking causes social costs of 79 billion euros per year [3].

Although the health risks of smoking are well known, around 28% of the population were reported to smoke in 2016 and 2017 in Germany [4]. Similar to other developed countries [5], smoking is not equally present among all demographics, but has become increasingly concentrated among low income population groups. For instance, from 1998 to 2014, the prevalence of smoking decreased in most income groups, whereas it increased to nearly 34% among the population group in the lowest income quartile [6]. Over the last decades, socio-economic differences in smoking behaviours have become one of the major contributors to existing socio-economic disparities in quality of life, morbidity and mortality [7, 8].

One population group at a particularly high risk of smoking is food pantry users. Food pantries are charitable organizations that distribute surplus food donated from food banks, retail stores, and manufacturers to those in need [9]. Although food pantry users are heterogeneous in terms of their educational background, age, and household size, one commonality is low income [10]. In previous studies in Germany, the prevalence of smoking was higher among participating food pantry users, at around 37% [11] and 47% [12], compared to others with low income. Similar or even higher smoking prevalence was found among food pantry users in other European countries [13, 14].

An additional concern is the observed high prevalence of food insecurity among food pantry users [11, 13–15]. Food insecurity exists “whenever the availability of nutritionally adequate and safe foods or the ability to acquire acceptable foods in socially acceptable ways is limited or uncertain” [16]. Food insecurity is related to dietary quality [17, 18] as well as the risk of several chronic diseases such as obesity, diabetes mellitus and depression [19, 20]. In a previous German study, around 70% of over 1000 food pantry users were reported to be food insecure, of which around 28% were moderately and 8% were severely food insecure [11]. In contrast, the Food and Agriculture Organization of the United Nations estimated that around 4% of the population was mildly or severely food insecure in Germany [21].

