## Objectives and hypotheses of the study

The main objective of the study is to investigate the impact of the smoking cessation measures on the smoking prevalence and on food security among food pantry users in Berlin.

The following primary hypotheses will be tested:
The percentage of individuals displaying continuous smoking abstinence 6 months after the treatment will be higher in the intervention condition compared to the control condition.The percentage of participants with an improved food security level 6 months after the treatment will be higher in the intervention condition compared to the control condition.The increased food security level will be mediated by continuous smoking abstinence.

Important secondary objectives include
to assess the impact of the smoking cessation measures on other measures of smoking status (point prevalence of smoking abstinence, the mean number of cigarettes smoked per day) and of food insecurity (the mean number of affirmative responses on the FIES) as well as on the health-related quality of life scores and body-mass-index;to investigate whether possible intervention effects are moderated by demographics (age, gender, migration status, socioeconomic status), the nicotine dependence and time perspective.

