### Study population

The study population will include users of any of the participating food pantries who reported smoking at least one cigarette or cigarillo per day. Participants must be at least 18 years old and able to sufficiently understand and speak German. Exclusion criteria includes non-smokers and individuals who smoke less than daily as well as individuals who do not use any of the participating food pantries. In addition, individuals who are 17 years of age or less, are unable to understand and speak German, or are illiterate, will also be excluded. Finally, individuals who only use e-cigarettes or tobacco heating systems will be excluded, since the impact of the original “Rauchfrei” program on this form of tobacco consumption is currently unknown.

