### Statistical analyses

The data will be analysed using the intention-to-treat principle, therefore including all participants irrespective of any dropouts after the baseline assessment. Missing values among the intention-to-treat population will be imputed using the baseline observation carried forward technique.

The mean, standard deviation, minimum and maximum will be given for continuous variables. Frequencies will be given for categorical variables.

To investigate differences between the intervention and the control group, independent t-tests for continuous variables and chi-square tests for categorical variables will be used. To test hypotheses 1 and 2, differences in the prolonged smoking abstinence and food insecurity improvement (the percentage of participants with an improved food security level) between the intervention and control group will be investigated using the chi-square test adjusted for intraclass correlation within clusters [50]. To account for the nesting of participants within the food pantry, mixed models with the logit link function will be used to predict cessation and food security improvement. To test hypothesis 3, a structural equation model will be used [51]. This identifies if the intervention condition predicts smoking cessation (path A), if smoking cessation predicts improvement in food security level (path B), if the intervention condition predicts the improvement in food security level (path C), and if the impact of the intervention condition on the improved food security level will be attenuated when controlling for smoking cessation.

Secondary outcomes will be analyzed accordingly.

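### The second primary outcome counts participants who are food secure at baseline and cannot improve, which shrinks the hypothesis 2 risk difference, weakens path B of hypothesis 3 and costs some power

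*Protocol article*

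**What the plan says.** Under Outcomes, the second primary outcome is "increased food security level (the percentage of participants with an improved food security level) 6 months after the treatment has finished". The same section sets the scale: "Food insecurity is categorised into four groups: food security; mild food insecurity; moderate food insecurity; and severe food insecurity". Hypothesis 2 is worded to match: "The percentage of participants with an improved food security level 6 months after the treatment will be higher in the intervention condition".

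Under Study population, participants are "users of any of the participating food pantries who reported smoking at least one cigarette or cigarillo per day", adults who understand German. Food insecurity is not an entry criterion. The Background reports that in an earlier German study "around 70% of over 1000 food pantry users were reported to be food insecure".

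Under Statistical analyses, the data are analysed by intention to treat, "therefore including all participants irrespective of any dropouts after the baseline assessment", and "Missing values among the intention-to-treat population will be imputed using the baseline observation carried forward technique". Hypotheses 1 and 2 "will be investigated using the chi-square test adjusted for intraclass correlation within clusters". A logit mixed model is also planned, and a structural equation model for hypothesis 3. No baseline food security term, stratum or restricted set is named for any of these, and the randomisation section names no stratification.

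**The concern.** A participant at the best level at t0 is scored as not improved whatever happens afterwards, in either arm. Such participants stay in the denominator of hypothesis 2 and in the outcome of hypothesis 3, but they carry no information on whether the programme relieves food insecurity.

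Three things follow. The reported difference in percentages understates the effect among people who could benefit. Some power is lost. In hypothesis 3, a quitter who was already food secure is recorded as a quitter without improvement, which pulls path B (cessation to improvement) towards zero.

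This goes beyond a detail that an article leaves to the analysis plan: the outcome, its denominator and the test are all stated here.

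**Working it through.** **Inputs from the protocol.** 416 participants in 32 pantries, 1:1, so 208 per arm; 13 per pantry; ICC 0.02; 5% significance level (sidedness not stated); cessation 10% against 3%; about 70% of pantry users food insecure.

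**Assumptions.** The protocol gives no improvement rates and no sample size for hypothesis 2. Improvement rates among those able to improve are therefore assumed: control *b* = 10 to 40%, effect *d* = 7, 10 or 15 points. The food-insecure share *f* is varied from 60 to 90%. Tests are two-sided at 5%.

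**The plan's own figure.** Design effect 1 + 12 × 0.02 = 1.24. Pantries per arm = (t₀.₉₅ + t₀.₈₀)² × (0.10 × 0.90 + 0.03 × 0.97) × 1.24 / (13 × 0.07²), iterated on 2(k − 1) degrees of freedom. This gives 15.1, rounded up to 16 per arm: 32 pantries and 416 participants. The stated figure is reproduced, but with a one-sided 5% test; a two-sided test gives 19.2, so 20 per arm. That is a separate matter. The figure concerns hypothesis 1 only.

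**Dilution.** The rates over all participants are *f·b* and *f·(b + d)*, so the risk difference is *f·d*. At *f* = 0.70, 0.30 × 416 ≈ 125 participants cannot improve and 10 points becomes 7. The factor is 0.6, 0.8 or 0.9 at *f* = 60, 80 or 90%. This applies to the difference in percentages. The risk ratio is unchanged (0.21/0.14 = 0.30/0.20 = 1.5), and the odds ratio moves little (1.71 to 1.63).

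**Power.** Power = Φ[(δ − 1.96·SE₀)/SE₁], where δ is the risk difference in the set analysed, SE₀ the pooled and SE₁ the unpooled standard error.
- All participants: effective n per arm = 208/1.24 = 167.7.
- Food insecure only, at *f* = 0.70: 145.6 per arm, 9.1 per pantry, design effect 1 + 8.1 × 0.02 = 1.162, effective n = 125.3.
- Example, 20% against 30%. All: rates 14% and 21%, (0.07 − 1.96 × 0.0415)/0.0413 = −0.27, power 39%. Restricted: (0.10 − 1.96 × 0.0547)/0.0543 = −0.13, power 45%.

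Power at *f* = 0.70, all participants then restricted:

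| Effect among those able to improve | control 10% | control 20% | control 30% | control 40% |
|---|---|---|---|---|
| 7 points | 33.5 / 36.7 | 22.6 / 25.6 | 18.3 / 21.5 | 16.2 / 19.9 |
| 10 points | 55.3 / 60.2 | 39.2 / 44.7 | 31.9 / 38.1 | 28.0 / 35.5 |
| 15 points | 83.8 / 88.3 | 68.6 / 76.1 | 59.0 / 69.1 | 53.3 / 66.4 |

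The gain is about 3 points for a 7-point effect and 5 to 6 for a 10-point effect (control 10 to 30%; 3.7 and 7.5 at 40%). It is 8 to 13 for a 15-point effect (control 20 to 40%; 4.5 at 10%). For 20% against 30% at other shares: 33.6 / 40.1 at *f* = 60%, 44.9 / 48.9 at 80%, 50.6 / 52.7 at 90%.

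These gains use ICC 0.02 in both analyses. If 0.02 holds among the food insecure, the diluted outcome has a smaller ICC. At a mean rate of 25% it is 0.49 × 0.02 × 0.1875 / (0.175 × 0.825) = 0.013, and the example becomes 42% against 45%. A simulation of the same example gave 39.5% against 41.3%. The direction holds, but the gain may be nearer 2 to 3 points there.

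**Hypothesis 3.** At the planned cessation rates, 0.10 × 208 + 0.03 × 208 ≈ 27 participants quit. If quitting is unrelated to food security, about 0.30 × 27 ≈ 8 of them cannot improve, and the path B difference in improvement is again about 0.7 of its value among those able to improve.

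**Chance imbalance.** The SE of the between-arm difference in the food-insecure share is √(2 × 0.7 × 0.3 × 1.24/208) = 0.050, a 95% range of about ±9.8 points. If 20 to 30% of the food insecure improve, this moves the difference by ±2.0 to ±2.9 points. In simulation under no effect the rejection rate was 5.0%.

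**The case against.** **The effect may be too small for the change to matter.** The protocol's mechanism is that quitting frees money for food, and the planned cessation difference is 7 points. If the effect runs only through quitting, and quitting is unrelated to food security, it cannot exceed about 7 points among those able to improve. The change then gains about 3 points of power, and hypothesis 2 is weak either way. This stands. The larger gains need a 15-point effect that nothing in the protocol supports.

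**The 30% comes from another population.** The 70% covers all pantry users, while participants smoke daily, and the Background reports that smoking and food insecurity are related. The share at the ceiling may be lower. This stands as to size; at 90% food insecure the same problem remains, but smaller.

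**Counting everyone is a legitimate question in a pragmatic trial.** It asks what share of enrolled smoking pantry users improve when the programme is offered. The contrast is valid, so the all-participant result is worth reporting. It does not follow that it should be the primary test, since restriction gave more power in every case tried.

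**Chance imbalance.** A reader might infer that hypothesis 2 is biased by uneven numbers of food-insecure smokers in the arms. The documents do not support this. Such imbalance is ordinary sampling noise, already part of the test's standard error, and type I error stays at 5%.

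**The FIES mean.** The mean number of affirmative responses does not depend on crossing a level, but it is only a secondary outcome and does not repair the primary one.

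**Conclusion.** The ceiling is real on the protocol's text, and its consequences are modest. The hypothesis 2 risk difference is about 0.7 times the effect among those able to improve if 70% are food insecure, and 0.6 to 0.9 times over a range of 60 to 90%. Path B is weakened likewise. The power lost is a few points at effects the protocol's own mechanism makes plausible, and approaches 10 points or more only under larger assumed effects.

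This rests on assumed improvement rates, on carrying a figure for all pantry users over to daily smokers, and on ICC 0.02. Two stronger readings are not supported: that the comparison is invalid or its type I error inflated, and that a food-secure quitter is evidence against mediation. Such a quitter only dilutes path B. The change is worth making because it is cheap and makes the outcome answer the study's question.

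**What to change.** Define the analysis set for hypothesis 2, and for the food-security paths of hypothesis 3 (B and C), as randomised participants with mild, moderate or severe food insecurity on the t0 FIES. Keep all participants for hypothesis 1. Report the all-participant result for hypothesis 2 as supportive, and worsening among those food secure at t0 as a secondary outcome.

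The FIES is already completed at t0, before participants are told their pantry's allocation and while staff are blinded. Restricting on it therefore keeps the randomised comparison, provided that blinding holds.

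The cost is wording only, with no new data. The downside is that the estimate then applies to food-insecure smokers only and uses fewer participants (about 291 of 416 at 70%), and hypothesis 2 may still have low power.

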### Pre-study: stakeholder engagement to develop the intervention

Before starting the cluster randomised controlled trial, stakeholders will be engaged to develop a behavioural group counselling program for smoking cessation adapted to the needs of the food pantry users. The interventional group program is planned to be based on the existing evidence-based behavioural counselling smoking cessation program called “Rauchfrei” (“smokefree”) [34]. The needs of the food pantry users will be explored qualitatively in interviews and group discussions.

The original “Rauchfrei” program was developed by the Institute for Therapy Research in Munich and the German Federal Centre for Health Education (Bundeszentrale für gesundheitliche Aufklärung) and is the most widespread cognitive behavioural group program for smoking cessation in Germany [34]. The original program consists of 3 to 6 weekly meetings with other participants and the “Rauchfrei” trainer along with individual telephone-based counselling [35].

The methods of behavioural modification used consisted of cognitive strategies to change attitudes, motivational interviewing, strategies of goal orientation, and psychoeducation as well as the development of coping skills to deal with cravings and relapses. The program includes a fixed date to quit smoking in the middle of the program [35].

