### Study design

After the pre-study, a pragmatic two-arm cluster randomised controlled trial, targeting approximately 32 food pantries in Berlin, will be conducted. Cluster randomisation is used to minimise the risk of carryover effects from the intervention to the control group. Data among food pantry users will be assessed on the date of study inclusion (t0), 1 month after completing the smoking cessation program (t1), and 6 months after completing the smoking cessation program (t2) (see Fig. 1). The control group will receive the smoking cessation program after the intervention group has completed the program (waiting list control group).

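### The primary abstinence outcome runs from the participant's last quit attempt with no minimum duration, so it cannot separate recent re-quitters from people abstinent through the six months after treatment

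*Protocol article*

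**What the plan says.** All references are to the Protocol article.

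- **Objectives and hypotheses of the study.** Hypothesis 1 reads: "The percentage of individuals displaying continuous smoking abstinence 6 months after the treatment will be higher in the intervention condition" than in the control condition. Hypothesis 3 makes the same abstinence variable the mediator of improved food security.
- **Study design.** t1 is one month after the programme; t2 is "6 months after completing the smoking cessation program (t2").
- **Outcomes.** Primary abstinence is self-reported cessation, at most 5 cigarettes "since the start date of their last attempt to quit", and it is "validated by the exhaled carbon monoxide test (< 10 ppm of carbon monoxide"). Point prevalence of abstinence is listed separately as a secondary outcome.
- **Measures.** The item used at t1 and t2 begins "Have you smoked at all since [start date of last attempt to quit"], with three answers: not a puff, 1–5 cigarettes, more than 5. CO is measured at baseline, t1 and t2.
- **Statistical analyses.** The primary variable is called *prolonged* abstinence.
- **Pre-study.** Of the original programme on which the intervention will be based: "The program includes a fixed date to quit smoking in the middle of the program".
- **Control.** The waiting-list arm "will receive the intervention when the last data collection period is finished (after t2").

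**The concern.** The name of the outcome and its rule describe different things. Hypothesis 1 and the analysis section speak of abstinence that lasts. The rule and the questionnaire item start the clock at whichever quit attempt came last, however recent. Nothing links that attempt to the programme's quit date, to the end of the programme or to t1, and nothing sets how long it must have lasted.

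At stake is what a positive result would mean. If recent re-quitters count as successes, the primary outcome moves towards the point-prevalence measure that the plan treats as secondary, and a claim of sustained cessation would not be supported. The mediation analysis for hypothesis 3 inherits the problem. Its argument, set out in the Background, is that money no longer spent on tobacco becomes available for food, and an attempt that began days before t2 has had little time to do that.

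**Working it through.** **1. Applying the rule as written.** Take a participant who relapses after the programme, answers more than 5 cigarettes at t1, smokes for months and starts a new attempt a few days before t2.

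- Cigarettes since the last attempt: 0, so the item is answered not a puff and the ≤ 5 limit is met.
- CO at t2: if below 10 ppm, validation is met. CO is measured only at the visits, so it says nothing about the months between t1 and t2.
- t1 record: it contradicts continuous abstinence, but no stated rule uses it.

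Result: continuously abstinent at t2. The same code goes to a participant with no cigarettes since the programme, and the t2 item gathers nothing that separates the two.

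**2. Reproducing the plan's sample size.** Inputs from Sample size: 10% vs 3%, ICC 0.02, 13 participants per cluster, 5% level, 80% power, 16 clusters per arm. Sidedness is not stated.

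- Design effect = 1 + (13 − 1) × 0.02 = 1.24.
- Variance sum = 0.10 × 0.90 + 0.03 × 0.97 = 0.1191.
- Clusters per arm = (t₁₋α + t₀.₈)² × 0.1191 × 1.24 / (13 × 0.07²).
- One-sided 5%, 30 df: (1.697 + 0.854)² × 0.1477 / 0.0637 = 15.09, rounded up to 16 per arm. This gives the stated 32 clusters and 32 × 13 = 416 participants.
- Two-sided: 18.2 per arm with z and 19.2 with t, that is 19 or 20.

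Of the variants tried, only the one-sided t version gives 16. Both versions are shown below so that sidedness is not confused with the abstinence definition.

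**3. Illustration: recent quitters counted equally in both arms.** Assume d extra points in each arm on top of 10% vs 3%. The documents give no value for d. With 16 × 13 = 208 per arm:

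SE = √{[p₁(1 − p₁) + p₂(1 − p₂)] × 1.24 / 208}

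Power = P(T₃₀ < Δ/SE − 1.697) for the one-sided t version, or Φ(Δ/SE − 1.960) for the two-sided z version.

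| d (points) | Rates | Δ (points) | SE | Δ/SE | One-sided t | Two-sided z |
|---|---|---|---|---|---|---|
| 0 | 10% vs 3% | 7 | 0.0267 | 2.63 | 82% | 75% |
| 1 | 11% vs 4% | 7 | 0.0285 | 2.46 | 77% | 69% |
| 2 | 12% vs 5% | 7 | 0.0302 | 2.32 | 73% | 64% |
| 3 | 13% vs 6% | 7 | 0.0318 | 2.20 | 69% | 60% |

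The difference stays at 7 points; only the variance rises.

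**4. Illustration: extra points in one arm only (2 points, assumed; two-sided z).**

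- Controls only, 10% vs 5%: Δ = 5 points, SE 0.0286, power about 42% (one-sided t about 52%).
- Intervention only, 12% vs 3%: Δ = 9 points, SE 0.0283, power about 89%.

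The effect can go either way, depending on where the late attempts fall.

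**The case against.** **The cited standard may settle it.** Measures and Outcomes both cite a published abstinence standard, and the date in the item is a bracketed placeholder that staff might fill with the programme quit date. The standard is not among the documents, so this cannot be excluded. It does not outweigh the explicit text: the Outcomes section says the participant's own last attempt, and the item repeats it.

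**Hypothesis 1 is still measured.** A reader might infer that it is not measured at all. That goes too far. Participants abstinent since the programme are captured; they are mixed with recent re-quitters and cannot be told apart from them. This objection stands.

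**The anchor need not differ by arm in a known direction.** A reader might infer that intervention participants have a fixed quit date while any recent attempt serves for controls, so the contrast must shrink. The fixed date is described for the original programme, and the trial programme is still to be designed. Strengths and limitations says waiting-list participants may put off their efforts to change, so late attempts could as well fall in the intervention arm, which has counselling and nicotine replacement. This objection stands: no direction can be claimed.

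**The planning rates may not be long-term rates.** The Sample size section says only cessation rates, from a source not at hand. That 10% vs 3% no longer describe the outcome therefore cannot be shown.

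**The size is assumed.** Correct. The shortfall at 75% without any misclassification comes from using a two-sided test, not from the abstinence definition.

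**Conclusion.** The point holds in limited form. As defined in Outcomes and asked in Measures, primary abstinence has no minimum duration and no study-based start. It therefore does not establish the continuous or prolonged abstinence named in hypothesis 1 and in Statistical analyses. It moves towards the secondary point-prevalence outcome and passes into the mediator of hypothesis 3. This follows from the wording alone and needs no numerical assumption.

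The effect on the treatment contrast is unknown in both direction and size. The power figures above rest on an assumed 1 to 3 points of recent quitters and on the plan's own rates, ICC and cluster size. They show that even misclassification balanced between the arms would cost about 5 to 13 percentage points of power on the one-sided t calculation (82% to 77–69%). They do not show that it will occur.

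**What to change.** 1. Define the primary outcome as at most 5 cigarettes in total over one common window ending at t2, for example from programme end, with a stated grace period, to t2.
2. Use the same elapsed window for control pantries, tied to their t1/t2 visit schedule.
3. Reword the t1/t2 item so that it asks about smoking since the start of that window.
4. Count as non-abstinent anyone whose t1 answer or t1 CO, within the window, contradicts the claim. Keep CO below 10 ppm at t2.
5. Report abstinence since the last attempt as a separate sensitivity outcome, not under point prevalence.
6. Use one term for the outcome in the hypotheses, Outcomes and Statistical analyses.

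Cost: one reworded item, one definition and a window date for each pantry; the t1 data are already planned. The item must be changed before follow-up begins, because later analysis cannot recover smoking history that was not asked about. Observed rates will be lower in both arms, and controls who quit later inside the window will count as non-abstinent. The sensitivity outcome shows how much that matters.
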